### Data collection and management

All data will be collected and managed using the Research electronic data capture (REDCap) system [44]. The data will be entered into the REDCap Database by a dependent researcher, then double checked by a second researcher. The statistician will review the database to ensure accurate data collection and correct data export for future analyses. All data will either be kept in a secure and lock-protected location and be backed up in different network drives.

### Investigator training and quality control

We will hold expert consultation meetings to formulate Standard Operating Procedure (SOP) of this study. After that all researchers involved in this study will receive theoretical and practical training courses based on SOP to ensure this trial completely standardized. The training will include how to screen the eligible participants, instruct participants to complete the diary, complete the CRF and assess SF-36 and safety. To ensure the high-quality of this study, quality control assessment will be carried out every month. A specially trained medical officer will inspect the study.

### Statistical analysis

The statistical analysis will be carried out using SPSS statistical package (version 25.0). Data will expressed as mean ± standard deviations. All primary and secondary analyses will be analyzed based on intention-to-treat. Missing data will be filled by Last Observation Carry Forward rules. Demographic characteristics and other baseline values will be described using descriptive statistics. Baseline characteristics of participants will be compared using chi-square test for enumeration data and one-way analysis of variance for continuous variables. For the primary outcome, we will run a comparison between Tai Chi group, walking group and waiting list control group to figure out whether exercise is more effective for this condition. We will then run another comparison between Tai Chi group and walking group to figure out whether Tai Chi is more efficacious for hypertension. The above analysis will be performed using the ANCOVA model, age, pre-intervention BP, duration of hypertension, and family history of hypertension will be used as covariate [45]. Difference between the groups was calculated as mean differences or odds ratios alongside with their 95% confidence intervals. Multiple comparisons between the groups will be adjusted according to the Bonferroni correction method. The correlational analysis of BP and endothelial function factors will be conducted using Chi-square test. We will perform subgroup analyses based on whether patients are on antihypertensive medication to separate the effect size of Tai Chi.

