## Methods/design

### Design and setting

This is an open-label single-center RCT with 3 parallel arms. This trial has been approved by the regional ethical review committee of traditional Chinese medicine in Sichuan Province in March 2019 (reference number: 2019KL-001). We will compare Tai Chi with walking and waiting-list control. The trial will be conducted in the Hospital of Chengdu University of Traditional Chinese Medicine. The whole study period is 25 weeks, with 1-week baseline, 12-week intervention phase and 12-week follow-up phase. After randomization, participants in Tai Chi group and walking group will receive exercise training 3 times per week for continuous 12 weeks. Participants in waiting-list group can decide whether or not to receive exercise training after follow-up period. Outcomes will be measured at baseline, 12 weeks and 24 weeks after randomization. All participants will be required to sign the written informed consent before randomization. This protocol was compiled in line with the SPIRIT 2013 [29] (Table 1). The flow diagram of this trial is presented in Fig. 1.

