### Outcome measurements

#### Primary outcome

The primary outcome in our study is the change in average 24-h SBP between baseline and 12-week after randomization. Ambulatory blood pressure monitoring (ABPM) will be used to assess the BP level. Participants will wear ABPM kit (Space Labs Medical, ABP Monitor 90,217, Redmond, WA, USA) and maintain their usual activities during the monitoring period, while avoiding strenuous exercise. During a 24-h monitoring period, automatic inflation measurement will be taken every 15 min during daytime (07:00 to 22:59) and every 30 min during night-time (22:59 to 07:00). The 24-h ABPM will be measured at baseline, 12 weeks and 24 weeks after randomization. Participants will be asked to record the time to wake up and go to bed in their self-dairies.

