#### Secondary outcomes

The average 24-h DBP, average SBP and average DBP during the daytime and night-time, BP variability, SBP load and DBP load, circadian rhythm of BP, and morning BP surge measured by ABPM will be considered as secondary outcomes.

Endothelial dysfunction is associated with hypertension and its presence correlates with target organ damage. Furthermore, endothelial dysfunction may be both a cause and a consequence of hypertension [41]. Therefore, the change of serum concentrations of Nitric Oxide (NO), endothelin (ET), thromboxane A2(TXA2), vascular endothelial growth factor (VEGF) will be tested to measure the endothelial function using commercial ELISA kits (Bender Med-Systems, Vienna, Austria). Blood samples of participants will be collected at baseline and 12 weeks after randomization.

Home blood pressure monitoring (HBPM) is a self-monitoring tool that can be incorporated into the care for patients with hypertension. Patients will use automated blood pressure monitors (AND, UA-767PBT; Shenzhen, China) to measure BP at home. HBPM will be conducted according to 2019 Chinese Hypertension League guidelines on home blood pressure monitoring [42] during the whole trial. At baseline, patients will measure BP at home every morning (6:00–9:00) and evening (18:00–21:00), 3 times per measurement for 7 days. During intervention and follow-up, patients will measure BP at home every Monday morning (6:00–9:00) and evening (18,00–21:00), 3 times per measurement [42]. Meanwhile, participants will be asked to record BP value in their self-dairies.

Changes in patients’ health-related quality of life will also be assessed according to the Medical Outcomes Study 36-Item Short Form (SF-36) questionnaire Chinese version [43]. This scale contains eight dimensions (physical function, role physical, bodily pain, general health, vitality, social function, role emotional, mental health) and two summary components (physical and mental), with score from 0 to 100. High scores indicate a better quality of life. SF-36 will be measured at baseline and 12 weeks after randomization.

For participants with antihypertensive medication, they will be asked to record the frequency, dosage and types of medication in their self-dairies.

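### For the week-12 primary outcome, LOCF amounts to carrying the baseline forward: every participant without a week-12 ambulatory recording is assigned a change of exactly zero

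*Protocol article*

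**What the plan says.** The Statistical analysis section gives one rule for missing values, without exception: "Missing data will be filled by Last Observation Carry Forward rules". It applies to the planned ANCOVA on all randomised participants: "All primary and secondary analyses will be analyzed based on intention-to-treat".

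The Primary outcome section defines the endpoint: "The primary outcome in our study is the change in average 24-h SBP between baseline and 12-week after randomization". It also fixes the ambulatory schedule: "The 24-h ABPM will be measured at baseline, 12 weeks and 24 weeks after randomization". Design and setting gives the same three time points for outcomes in general: "Outcomes will be measured at baseline, 12 weeks and 24 weeks after randomization".

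Under Secondary outcomes, two outcome groups have only one post-baseline measurement: "SF-36 will be measured at baseline and 12 weeks after randomization" and "Blood samples of participants will be collected at baseline and 12 weeks after randomization". Home BP differs, because it is measured weekly throughout intervention and follow-up.

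The Sample size section allows for 20% drop-out, sets the SD at 20 and enrols 78 per arm.

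**The concern.** LOCF is usually understood as carrying the latest on-treatment value forward. On this schedule it cannot do that for the primary outcome, because the only value before week 12 is the baseline. The rule therefore assumes that every participant without a week-12 recording had no change, whatever the arm. The protocol gives no reason for that assumption.

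The primary estimate and its interval are at stake. The protocol expects one participant in five to drop out. The trial is open-label, with two exercise arms and a waiting list, so drop-out could differ between arms. Zero-change values would then enter the arms in different proportions, which matters most for the named comparison of Tai Chi with walking, where the true difference may be small.

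SF-36 and the endothelial markers have the same problem. For week-24 ambulatory BP the assumption is different. Someone lost after week 12 has the week-12 value carried forward, so the effect is taken to persist, while someone lost before week 12 is carried at baseline. Both bear on the aim, stated in the Background, of observing the long-term effect.

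**Working it through.** **Inputs from the protocol article.** Ambulatory readings at 0, 12 and 24 weeks; endpoint at week 12; 78 per arm; SD 20; drop-out 20%. The enrolment figure is 195 × 1.20 = 234, or 78 per arm. A 20% loss from 78 is 15.6, leaving 62.4 per arm with data. The protocol gives no figure that depends on LOCF, so there is none to reproduce.

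**Assumptions not in the documents.** Missing at random within arm; correlation of 0.5 between baseline and week 12; SD 12 as an alternative to 20; unequal drop-out rates; true differences chosen for illustration.

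**Step 1: imputed value.** For a participant missing week 12, the imputed change is baseline − baseline = 0.

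**Step 2: expected estimate.** With true mean change μ and missing fraction d, the expected arm mean under LOCF is (1 − d)μ. With d = 0.20 in both arms:
- true difference 10 mmHg: 0.8 × 10 = 8.0;
- true difference 16.7 mmHg: 0.8 × 16.7 = 13.4. The 16.7 is 3.37 − (−13.33), if the three means under Sample size are read as arm values. That sentence is ambiguous, so the reading is an assumption.

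**Step 3: standard error, unadjusted, SD 20, changes of −10 and 0, d = 0.20.**
- Observed data only: 20 × √(2/62.4) = 3.58.
- All 78 per arm fully observed: 20 × √(2/78) = 3.20.
- LOCF: the variance per arm is (1 − d)SD² + d(1 − d)μ², that is 320 + 16 = 336 and 320. SE = √(656/78) = 2.90.

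The LOCF analysis thus reports more precision than complete follow-up would have given.

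**Step 4: coverage and rejection.** Simulated two-arm ANCOVA on baseline, 78 per arm, correlation 0.5, test at an unadjusted 5%:

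| Truth | Missing | LOCF estimate | Result, SD 20 | Result, SD 12 |
|---|---|---|---|---|
| Difference 10 mmHg | 20% v 20% | 8.0 | CI coverage about 88% | about 77% |
| Both arms −10 | 20% v 20% | 0 | rejection about 5% | about 5% |
| Both arms −10 | 15% v 25% | 1.0 | rejection 6–7% | about 9% |
| Both arms −10 | 10% v 30% | 2.0 | rejection about 12% | about 23% |

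ANCOVA on observed data gives coverage of about 95% and rejection of about 5% throughout. The false differences follow from step 2: 10 × (0.25 − 0.15) = 1.0 and 10 × (0.30 − 0.10) = 2.0. If the protocol's Bonferroni correction means three tests at 0.05/3 = 1.67%, rejection in the last row is about 5% (SD 20) to 12% (SD 12), against 1.67% nominal.

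**Step 5: Tai Chi v walking.** On the arm-mean reading the planned difference is −13.33 − (−12.46) = −0.87.
- 10% missing in Tai Chi, 30% in walking: 0.9 × (−13.33) − 0.7 × (−12.46) = −3.28.
- The reverse: 0.7 × (−13.33) − 0.9 × (−12.46) = +1.88.

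Unequal drop-out alone can therefore change the sign.

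**The case against.** The strongest reply is that the figures above assume missing at random, so that drop-outs would have had their arm's full change. Under intention-to-treat, someone who stops exercising may well drift back to baseline. If drop-outs truly show no change, the 16.7 mmHg case has a true intention-to-treat difference of 13.4. LOCF then recovers it, and an observed-data analysis overstates it at about 16.7. This stands. The documents do not show which assumption is nearer the truth. The fair criticism is that the rule makes one strong assumption without justification, and the fix has to allow for the alternative.

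Three further points stand in part.
- With equal drop-out the estimate is pulled towards no effect, which is cautious for a superiority hypothesis. Power hardly moves (0.87 against 0.89 for a 10 mmHg effect at SD 20). The harm there is bias and poor coverage.
- The protocol gives a single 20% rate and predicts no imbalance. The unequal rates and SD 12 are illustrations, and the milder scenario gives only 6–9% rejection.
- A fuller analysis plan may contain sensitivity analyses, so their absence from the article is no finding. The LOCF rule itself is stated.

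A reader might also infer that LOCF makes the test invalid whatever the drop-out pattern, or that the model's SE is miscalculated. Neither is supported. With equal drop-out the null rejection rate stays near 5%. The model SE agrees with the LOCF estimator's own sampling SD (2.67 against 2.65 in one simulation of the 16.7 mmHg case at SD 20). It is small only relative to the information actually observed. Nor is LOCF baseline-carried-forward for every outcome, since weekly home BP usually supplies a later value.

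**Conclusion.** The concern holds for outcomes whose first post-baseline measurement is week 12: the primary ambulatory SBP change, the other week-12 ambulatory measures, SF-36 and the endothelial markers. There LOCF imputes exactly no change and treats it as data. A related but different assumption, persistence of the week-12 value, affects week-24 ambulatory BP for those lost after week 12.

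Under missing at random within arm, the protocol's own 20% drop-out, if equal, shrinks every difference by a fifth and lowers coverage of a 10 mmHg difference to about 88% (SD 20) or 77% (assumed SD 12). If drop-out differs between arms the bias can go either way, by 1.0 to 2.0 mmHg in the scenarios shown. That exceeds the 0.87 mmHg planning difference between Tai Chi and walking on the arm-mean reading. These sizes depend on the missingness mechanism, the correlation of 0.5 and the chosen rates. The zero imputation itself follows directly from the protocol's schedule.

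**What to change.** In the Statistical analysis section, replace LOCF for the primary analysis with a method that uses all observed data under missing at random.

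- **Ambulatory BP:** a mixed model for repeated measures at weeks 12 and 24, with arm by visit, baseline by visit and the covariates already listed. Alternatively, multiple imputation by arm followed by the planned ANCOVA.
- **SF-36 and endothelial markers:** these have only one post-baseline time point, so the two-visit model does not apply. Use multiple imputation by arm, or ANCOVA on observed data.
- **Sensitivity analysis:** keep baseline-carried-forward, or use a reference-based imputation, because drop-outs who stop exercising may return towards baseline. Name it as such, so that the zero-change assumption is visible.

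Weekly home BP needs its own rule and is outside this point.

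The cost is revised wording and a little more analysis work, with no new visits or participants. The CI widens: in the 16.7 mmHg case at SD 20, the adjusted SE from observed data is about 3.11, against 2.64 under LOCF.

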### Participants

#### Sample size

This study is an RCT, the intervention group is the Tai Chi group, and the control groups are walking group and waiting-list group. The reduction of Systolic Blood Pressure (SBP) is set as the primary outcome. According to previous study [31], the mean difference and standard deviation of SBP was − 13.33 ± 46.73, − 12.46 ± 33.37 and 3.37 ± 46.01 for Tai Chi compared with walking and waiting-list control. The sample size was calculated using One-Way analysis of variance, F-Tests with the PASS 15.0 software. The standard deviation is set as 20. A total of 65 participants per arm are needed to achieve a power of 80% at a significant level of 5%. A sample size of 195 participants is required to sufficiently detect a target effect size. Considering a 20% drop-out rate, we intend to enroll a total of 234 participants, with 78 participants in each group.

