## Discussion

In our previous systematic review of Tai Chi for hypertension, we found high heterogeneity and poor methodological quality in original RCTs [28]. Among the included trials, only a few trials reported the results of follow-up, the long-term effect of Tai Chi is unclear. Based on the above facts, we hypothesized that: Tai Chi is superior to waiting-list control and walking control in regulating BP of patients with essential hypertension. To test the hypothesis, we designed this trial with a waiting-list group as a blank control group, which will provide an untreated comparison for the Tai Chi group to determine whether it is effective. We will use walking with targeted intensity as active-control group. By comparing with the walking group, whether Tai Chi is better than active control in hypertensive patients will be determined. Our previous study found that intervention of Tai Chi for 12–24 weeks could significantly lower SBP and DBP than intervention < 12 weeks and intervention > 24 weeks [28]. Therefore, we planned 12 weeks of intervention period to determine the effect of Tai Chi.

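### The stated 80% power belongs to a three-group F-test; at the protocol's own planning means, Tai Chi versus walking has about 6% power, or 2 to 3% after Bonferroni

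*Protocol article*

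**What the plan says.** The Discussion gives a hypothesis in two parts: "we hypothesized that: Tai Chi is superior to waiting-list control and walking control in regulating BP of patients with essential hypertension". On the second part it adds: "By comparing with the walking group, whether Tai Chi is better than active control in hypertensive patients will be determined".

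The Statistical analysis section plans an ANCOVA on the primary outcome. It first compares all three groups, to learn whether exercise is more effective. Then: "We will then run another comparison between Tai Chi group and walking group to figure out whether Tai Chi is more efficacious for hypertension". It adds: "Multiple comparisons between the groups will be adjusted according to the Bonferroni correction method". The number of comparisons covered is not given.

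The Sample size section rests on a different test: "The sample size was calculated using One-Way analysis of variance, F-Tests with the PASS 15.0 software". Its planning values are "13.33 ± 46.73, − 12.46 ± 33.37 and 3.37 ± 46.01" (the first value also carries a minus sign in the text) for Tai Chi, walking and waiting list. Then "The standard deviation is set as 20", and the result is "A total of 65 participants per arm are needed to achieve a power of 80% at a significant level of 5" percent. No power is given for any pairwise comparison, and the sizing makes no allowance for Bonferroni.

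**The concern.** An F-test across three groups asks whether the three means differ at all. It tests neither part of the hypothesis. With Tai Chi and walking planned at almost the same value, its power comes from the distance of the waiting-list arm, so the 80% says nothing about Tai Chi versus walking. A significant F-test also does not by itself show that exercise works, because it does not say which groups differ.

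What is at stake is how the walking result can be read. If the planning means are right, the test against walking will almost certainly be non-significant, whether or not the small assumed benefit is real. The Bonferroni correction, left out of the sizing, may also take the efficacy contrast (Tai Chi versus waiting list) below the power the protocol states.

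**Working it through.** **Inputs.** From the Sample size section: mean changes −13.33 (Tai Chi), −12.46 (walking) and 3.37 as printed (waiting list); SD 20; 65 per arm; alpha 5%. From the Statistical analysis section: Bonferroni, number of comparisons not stated, so I use 2 (0.025) and 3 (0.0167). Assumptions: pairwise tests are two-sided, and the three values are group mean changes. The protocol words them loosely as mean differences, but the reading is supported in step 1.

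**1. Reproducing 65 per arm.** For a one-way ANOVA with three equal groups, the noncentrality is λ = n × Σ(μᵢ − μ̄)² / SD².

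- Third mean 3.37 as printed: μ̄ = −7.47, Σ = 176.7, λ = 65 × 176.7 / 400 = 28.7. Power is 99.9%, and 23 per arm would reach 80%. The plan's figure is not reproduced.
- Third mean −3.37: μ̄ = −9.72, Σ = 13.03 + 7.51 + 40.32 = 60.86, λ = 65 × 60.86 / 400 = 9.89. Power is 80.4% at 65 per arm and 79.8% at 64. The plan's figure is reproduced exactly.

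Alternative SDs with the printed means do not give 65 (33.37 gives 62; the pooled 42.5 gives 100).

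**2. What drives the F-test.** The Tai Chi–walking gap contributes 0.87² / 2 = 0.38 of the 60.86, or 0.6%. The rest comes from the waiting-list arm.

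**3. Tai Chi versus walking.** Difference = 13.33 − 12.46 = 0.87 mmHg. SE = 20 × √(2/65) = 3.51. Noncentrality = 0.87 / 3.51 = 0.248. From the noncentral t:

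| Two-sided alpha | Power at 0.87 mmHg | Difference detectable with 80% power |
|---|---|---|
| 0.05 | 5.7% | 9.9 mmHg |
| 0.025 | 2.9% | 10.9 mmHg |
| 0.0167 | 2.0% | 11.5 mmHg |

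These figures do not depend on the sign of 3.37. With all 78 enrolled per arm, power is 5.8%, 3.0% and 2.1%. For 80% power at 0.05 the trial would need 2 × ((1.960 + 0.842) × 20 / 0.87)² ≈ 8,300 per arm. The 95% CI half-width is 1.979 × 3.51 = 6.9 mmHg, so a significant result needs an observed difference about eight times the assumed one (6.94 / 0.87 = 8.0).

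**4. Allowing for ANCOVA.** Covariates with correlation ρ to the outcome shrink the SD to 20 × √(1 − ρ²). The protocol gives no ρ, so I take 0.3, 0.5 and 0.7.

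- Detectable difference at 0.05, 9.90 × √(1 − ρ²): 9.4, 8.6 and 7.1 mmHg.
- Power at 0.87 mmHg and 0.05: 5.8%, 5.9% and 6.4%.

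**5. Tai Chi versus waiting list.** With the third mean at −3.37, the difference is 13.33 − 3.37 = 9.96 mmHg. At SD 20 and 65 per arm, power is 80.5% at 0.05, 71.6% at 0.025 and 66.0% at 0.0167. With ρ = 0.3 (SD 19.1) it is 84.0%, 76.0% and 70.8%. With ρ = 0.5 (SD 17.3) it is 90.2%, 84.2% and 80.2%.

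**The case against.** **The true difference may exceed 0.87 mmHg.** This stands as a condition. A true 10 mmHg difference has 81% power at 0.05, and 5 mmHg has 29%. A reader might infer that the trial cannot resolve Tai Chi versus walking whatever the truth. The documents do not support that, only that it is far too small for the difference the protocol itself assumes. But the protocol names no larger target, and 10 mmHg is about the whole Tai Chi versus waiting-list effect on the reading that reproduces 65.

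**Tai Chi versus waiting list is planned.** A reader of the Statistical analysis section alone might conclude that it was left out. That goes too far: the Abstract and the Design and setting section announce the comparison, and the Discussion relies on it to judge effectiveness. The Bonferroni sentence naturally covers it. What remains is that the analysis section names only the walking contrast.

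**The efficacy contrast might look safe.** Taking 3.37 as printed, the difference is 16.7 mmHg and power is about 99% even at 0.0167. But those inputs also give the F-test 99.9% power, which contradicts the stated 80% at 65 per arm. The reassurance cannot be combined with the protocol's own sample size.

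**ANCOVA helps.** It does for the efficacy contrast: at ρ of about 0.5 or more it offsets even a three-way Bonferroni. It does almost nothing at 0.87 mmHg.

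**No equivalence claim is made.** True. The protocol already promises mean differences with 95% confidence intervals. Misreading a null result as equivalence is a risk to guard against, not something the protocol says.

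**An F-test followed by pairwise tests is common practice.** Also true. The fault is that the power of the first step is left to stand for the second.

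**Conclusion.** The point holds, conditional on the planning means. The 80% belongs to the three-group F-test and does not carry over to either pairwise hypothesis. At the assumed 0.87 mmHg, power against walking is 5.7% unadjusted and 2.9% or 2.0% after Bonferroni, and covariate adjustment leaves the unadjusted figure near 6%. Under those means the trial cannot support the Discussion's statement that superiority over walking will be settled.

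The second part rests on reading the third mean as −3.37, the only reading tried that returns 65. Bonferroni then leaves Tai Chi versus waiting list at 71.6% or 66.0%, below the stated 80%, unless the covariates explain enough variance to make up the loss.

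**What to change.** 1. **Statistical analysis.** In the one ANCOVA on the primary outcome, prespecify a fixed sequence, each test at two-sided 5%: first Tai Chi versus waiting list; then Tai Chi versus walking, tested only if the first is significant. State that this order replaces Bonferroni for these two contrasts. The first then keeps about 80% power with no added participants.
2. **The exercise question.** Keep walking versus waiting list (or both exercise arms versus none) as a named secondary contrast, so that whether exercise is more effective is still answered. Keep Bonferroni for the remaining comparisons.
3. **Sample size.** Confirm the sign of 3.37, say that the 80% refers to the F-test, and give the power or detectable difference for each contrast, with any assumed covariate correlation.
4. **Discussion.** Reword so that Tai Chi versus walking is read from its estimate and 95% CI, and say that non-significance will not be taken as equivalence.

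The cost is wording and test order, to be settled before outcomes are examined by group. The price is a more modest claim about walking, and no formal test against walking if the first contrast fails. The change does not raise the power against walking; it stops the protocol from promising what that power cannot deliver.

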### Allocation and randomization

Included participants will be randomly assigned to 3 groups (Tai Chi group, walking group, and waiting-list group) with 1:1:1 ratio. The randomization sequence will be created using R 3.5.1 by an independent statistician. The information of random numbers, allocation and intervention will be packed in opaque envelopes, and will be concealed to screeners and outcome assessors. A research assistant will inform eligible participants the allocation results through phone call after opening envelopes in order.

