#### Tai Chi exercise

Participants in Tai Chi group will be firstly instructed Yang style 24-form Tai Chi by the coaches with at least 5 years of teaching experience during the run-in period. After 3 days of teaching, coaches will assess the qualification of each participants based on: (1) accuracy of movement; (2) coordination and continuity of movement; (3) pauses times. Participants whose fluency and accuracy of Tai Chi movement reach over 60% with less than 5 times of pauses will be considered to be qualified. Unqualified patients will continue a 3-day teaching and a secondary evaluation. During the intervention period, qualified participants will receive a group-format exercise program, 3 sessions per week for 12 weeks. Each session will last 60 min, including a 10-min warm-up, a 40-min Tai Chi practice and a 10-min cool-down.

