#### Walking exercise

Using aerobic exercise to reduces BP has been confirmed [35, 36] and recommended in hypertension management guidelines [32, 37]. Walking is a simple and easy aerobic exercise for the elderly to do. We will use walking with targeted intensity as an active controlled. Walking group will be asked to walk, 3 sessions per week for 12 weeks. Each session will last 60 min, including a 10-min warm-up, a 40-min walking and a 10-min cool-down. To ensure the compliance of exercise, participants will be asked to record the start and end time of each exercise session in self-reported diaries.

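### Tai Chi is delivered in groups, but the sample size and the ANCOVA treat every participant as independent; if outcomes correlate within classes, both Tai Chi contrasts get standard errors that are too small

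*Protocol article*

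**What the plan says.** Allocation is at the level of the person (protocol article, Allocation and randomization): "Included participants will be randomly assigned to 3 groups (Tai Chi group, walking group, and waiting-list group) with 1:1:1 ratio".

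The arms then differ in delivery. Under Tai Chi exercise, "qualified participants will receive a group-format exercise program, 3 sessions per week for 12 weeks", which is 36 sessions; the abstract also calls the programme group-format. Under Walking exercise no class is described, and "participants will be asked to record the start and end time of each exercise session in self-reported diaries". Under Waiting list, no sessions take place during the intervention period.

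Sample size states: "The sample size was calculated using One-Way analysis of variance, F-Tests with the PASS 15.0 software". It adds "The standard deviation is set as 20" and "A total of 65 participants per arm are needed to achieve a power of 80% at a significant level of 5" percent. No design effect or between-class variance appears.

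Statistical analysis names the primary model: "The above analysis will be performed using the ANCOVA model, age, pre-intervention BP, duration of hypertension, and family history of hypertension will be used as" covariates. All four covariates describe the participant. That section specifies no class or coach term and no cluster-robust variance. It applies a Bonferroni correction to the comparisons between groups.

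**The concern.** People who train together share a time slot, a pace, group dynamics and probably an instructor, so their week-12 blood pressures may be more alike than those of people who never meet. With grouping in one arm of an individually randomised trial, the design is partially nested. An ordinary ANCOVA counts the 78 Tai Chi participants as 78 independent pieces of information. Under positive within-class correlation they carry less.

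The Discussion states two hypotheses: Tai Chi superior to waiting list, and Tai Chi superior to walking. Both use the grouped arm. If the correlation is there, both confidence intervals are too narrow, and a good or poor class can be read as an effect of Tai Chi itself. Bonferroni does not help, because it divides the significance level but starts from p-values that are already too small. Walking versus waiting list is unaffected if walking is done individually.

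**Working it through.** **Inputs from the protocol article:** 65 evaluable per arm, SD 20, 5% level, 80% power, one-way ANOVA F-test (Sample size); equal allocation (Allocation and randomization); ANCOVA with four participant-level covariates and Bonferroni (Statistical analysis).

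**Inputs assumed, because the document gives none:** 10 to 26 per Tai Chi class; ICC 0.01 to 0.10 (residual correlation within class, after covariates); walking unclustered; the same total variance in every arm.

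**The plan's own figure.** The "mean difference and standard deviation of SBP was" sentence gives −13.33, −12.46 and 3.37. Taken as the three arm means, their average is −7.47, the SD of the means is √(176.75/3) = 7.68, and f = 7.68/20 = 0.384. The noncentral F then needs 23 per arm for 80% power at 5%, so the stated 65 does not reproduce. That is a separate matter. It bears on this point only because the difference that 65 per arm was meant to detect is not recoverable, so no loss of power is quoted here.

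**Effect on the standard error.** With *m* per class, the design effect in the Tai Chi arm is DE = 1 + (m − 1) × ICC. Against an equal-sized unclustered arm, true SE / planned SE = √((1 + DE)/2). The number per arm cancels, so the ratio is the same at 65 and at 78.

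**Effect on the error rate.** Actual type I error = 2 × (1 − Φ(z / ratio)), with z = 1.96 for a nominal 5% test.

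Middle case, 13 per class and ICC 0.05:
- DE = 1 + 12 × 0.05 = 1.60
- ratio = √(2.60/2) = 1.14
- 1.96/1.14 = 1.72, so the actual error is 8.6%, and a nominal 95% interval covers about 91.4%

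Actual type I error of a nominal 5% test (DE in brackets):

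| Per class | ICC 0.01 | ICC 0.05 | ICC 0.10 |
|---|---|---|---|
| 10 | 5.5% (1.09) | 7.7% (1.45) | 10.4% (1.90) |
| 13 | 5.7% (1.12) | 8.6% (1.60) | 12.1% (2.20) |
| 20 | 6.1% (1.19) | 10.7% (1.95) | 16.0% (2.90) |
| 26 | 6.5% (1.25) | 12.4% (2.25) | 19.1% (3.50) |

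**Simulation check** (20,000 replicates, 65 per arm in five classes of 13, no covariates): 8.5% at ICC 0.05, 5.7% at ICC 0.01 and 4.7% at ICC 0. The three-arm F-test gave 8.3% at ICC 0.05.

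**Bonferroni.** The number of comparisons is not stated. With three as an example, the nominal level is 0.05/3 = 1.67%, and the actual rate in the middle case is 3.6%. The inflation carries through.

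**The case against.** **The size rests on assumed inputs.** This stands. On the protocol's SD of 20, ICC 0.01, 0.05 and 0.10 correspond to between-class SDs of 20 × √ICC = 2.0, 4.5 and 6.3 mmHg, and the upper values are large. The plan also restrains class effects: one centre, one routine, experienced coaches with a qualification test, a heart-rate target checked three times, monthly quality control and automated ambulatory measurement. That argues for the lower end of the range. It does not establish zero, and a model without a class term cannot show it.

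**A false positive against the waiting list needs odd circumstances.** The class effects would have to differ and yet average zero, so some classes would raise SBP. This is fair for that test. It does not apply to Tai Chi versus walking, where the null is only equal average benefit, nor to interval coverage, which is affected whatever the true mean difference.

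**The analysis plan may add a class term.** It may, but the article does not leave the model open. It names the method, lists the covariates and sizes the trial on independent observations.

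**Three inferences a reader might draw go too far.**
- That coaches lead all 36 sessions in fixed classes. The text places coaches in the teaching and assessment before the programme and does not say who leads the sessions or whether membership is fixed.
- That walking is certainly unclustered. The article describes no walking class, but it records session attendance for both exercise arms and gives them the same session structure.
- That the trial loses a known amount of power. Any such figure needs a target difference that the protocol never states.

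**Conclusion.** The point holds in conditional form. Group delivery in the Tai Chi arm and an independence-based sample size and ANCOVA are both in the text. For any positive within-class correlation, the planned standard errors of the two Tai Chi contrasts are too small. It would be wrong to say flatly that they are too small, because that depends on an ICC the document does not give: at ICC 0 nothing is wrong, and at ICC 0.01 a 5% test runs at 5.5% to 6.5%. Over the whole assumed range the figure is about 5.5% to 19%, with 8.6% in the middle case. These figures also assume that walking is done individually. The point deserves action because the exposure falls on both main hypotheses and the remedy is cheap.

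**What to change.** 1. Record each participant's Tai Chi class and coach in the CRF, beside the attendance already collected. Do this prospectively, since membership may be hard to reconstruct later.
2. In Statistical analysis, keep the same fixed effects and covariates but fit them in a partially nested linear mixed model. Give the Tai Chi arm a random class effect, treat each unclustered participant as a cluster of one, and use small-sample (for example Satterthwaite) degrees of freedom. If walking is also done in groups, give that arm its own class effect. The mixed-model procedure in SPSS, the package the plan names, can fit this.
3. In Sample size, state that the 80% power assumes no class effect.
4. State how the Tai Chi classes, and any walking groups, are formed. If all Tai Chi participants were in one class, no model could separate the class effect from the treatment effect.

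The cost is one CRF field, a few sentences, and modestly wider intervals for the Tai Chi contrasts. The change of model does not itself call for a different number of classes or a different way of delivering the sessions.
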